## Abstract

**Background:**

Patients with hypertrophic cardiomyopathy (HCM) are at increased risk of sudden cardiac death (SCD) due to ventricular arrhythmias and other arrhythmias. Screening for arrhythmias is mandatory to assess the individual SCD risk, but long-term electrocardiography (ECG) is rarely performed in routine clinical practice. Intensified monitoring may increase the detection rate of ventricular arrhythmias and identify more patients with an increased SCD risk who are potential candidates for the primary prophylactic implantation of an implantable cardioverter-defibrillator. To date, reliable data on the clinical benefit of prolonged arrhythmia monitoring in patients with HCM are rare.

**Objective:**

This prospective study aims to measure the prevalence of ventricular arrhythmias in patients with HCM observed by mobile health (mHealth)–based continuous rhythm monitoring over 14 days compared to standard practice (a 24- and 48-h long-term ECG). The frequency of ventricular arrhythmias in this 14-day period is compared with the frequency in the first 24 or 48 hours for the same patient (intraindividual comparison).

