### Recruitment

According to the sample size calculation (see Statistical Analysis section), recruiting 34 patients will be sufficient for the statistical analysis. Study participants will receive an echocardiography at rest and during exercise (bicycle ergometry) and a cMRI. In addition, their symptoms, family history, and premedication are collected, and their HCM Risk–SCD calculator score will be calculated. According to this score, patients are allocated to three risk groups: low risk (<4%), intermediate risk (4%-6%), and high risk (>6%) of SCD within 5 years. An ICD is generally recommended in the high-risk group, should be considered in the intermediate-risk group, and is not indicated for the low-risk group [1]. For this study, it is planned to recruit 17 patients with low and 17 with intermediate risk scores. All these patients will receive the 14-day ECG patch.

Patients with HCM between the ages of 18 and 75 years will be included if they have not yet undergone implantable loop recorder, pacemaker, or ICD implantation and if their estimated 5-year SCD risk according to the HCM Risk–SCD calculator score is <6%. A maximum age of 75 years was set as the upper limit, as SCD in patients with HCM mainly occurs at a young age [13]. Patients with a pre-existing cardiac implant (pacemaker, ICD, or implantable loop recorder) or an already accepted indication for it; Morbus Parkinson disease with relevant tremor; a transcoronary ablation of septal hypertrophy procedure in the last 4 weeks; inability to give informed consent; and current symptoms or a history of skin cancer, rash from skin adhesive, or dermatoses (contraindication to wearing the patch) are excluded.

A therapeutic procedure is established for the patient based on the information available to date. Afterward, an ECG patch is applied to the chest to continuously monitor the heart rhythm over 14 days. After completing the 14-day wearing period, patients should return the ECG patch. Any arrhythmias recorded will then be documented, and the therapeutic procedure will be re-evaluated with a recalculation of the HCM Risk–SCD calculator score.

An overview of the study process can be seen in Figure 1.

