### Outcomes

The rate of nsVT detection in the first 24 and 48 hours of monitoring versus the whole 14-day monitoring period will be compared. In addition, the prevalence of AF and other arrhythmias will be examined. Moreover, the results of the cMRI and, if applicable, the results of the genetic examination will be considered. The HCM Risk–SCD calculator score will be recalculated if new findings have occurred.

nsVT is defined as ≥3 consecutive ventricular beats at a rate of 120 beats per minute, lasting for <30 seconds [1]. AF is defined as atrial tachyarrhythmia lasting for >30 seconds [15]. The diagnosis of HCM is based on echocardiography; septum hypertrophy ≥15 mm in the absence of other causes of myocardial hypertrophy or septal or posterior wall thickness ratio >1.3 is required.

At the patients’ request, they will be informed about the rhythm-monitoring results and the resulting therapy changes after the ECG patch has been returned.

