### Dropout

If the patient wishes to discontinue participation in the study during the 14 days of wearing the device, this is possible at any time and without any disadvantages for the patient. In addition, according to patients’ preferences, they may not be informed about rhythm observations. The study physician should be informed about this and discontinuation. If a patient does not return the patch after the 14 days, this will be counted as a dropout.

In addition, a minimum duration of 288 hours has been established. If the ECG patch is worn for less than this time, exclusion from the study will occur. How long the patch has been worn can easily be determined based on the duration that ECG data is available.

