We hypothesize that prolonged rhythm monitoring will detect more arrhythmias than 24- or 48-hour monitoring. In a study with prolonged rhythm monitoring by Holter ECG over 14 days, 75% of patients with HCM had nsVT, compared with only 16.9% of patients in the first 24 hours [6]. However, it remains unclear if all these patients with nsVT should now receive an ICD. Previous studies have shown that patients who present with nsVT during 24-hour monitoring show it more frequently if monitoring is prolonged. Patients who showed nsVT later in the subsequent 14 days usually had only one episode [7]. Thus, it can be speculated that the detection of nsVT in a 24-hour monitoring period indicated more frequent spells of nsVT overall, with an associated higher SCD risk. Moreover, the rate and duration of nsVT vary, suggesting that longer and more rapid nsVT episodes indicate a higher SCD risk [6]. Prolonged monitoring may allow for the identification of patients with more frequent nsVT episodes, also taking into account the rate and duration of nsVT.

In addition, a correlation with late gadolinium enhancement load on cMRI will be investigated. If patients with high late gadolinium enhancement load show increased nsVT, these scar areas detected on cardiac MRIs could be identified as possibly pathogenic for the arrhythmias, and appropriate therapy (eg, ICD fitting) should be performed. This has so far not been investigated, so the results are needed.

In addition, the mHealth ECG patch method used here offers opportunities for other diseases as well. For example, patients with a stroke of unclear origin can be screened for AF over an extended period. It is also possible to capture intermittent subjectively perceived cardiac arrhythmias with the help of such an ECG patch, as this is often not possible with normal long-term ECGs.

In summary, prolonged mHealth-based rhythm monitoring will be used to investigate arrhythmia burden in patients with HCM. Increased detection of arrhythmias compared with 24-hour long-term ECG monitoring can be expected. It is essential to individually consider the rhythm monitoring results and optimize therapy accordingly. Findings of prolonged rhythm monitoring might be helpful in cases of borderline risk. A thorough discussion of the findings and possibly individual reassessment using the risk calculator could be an approach.

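### The 24/48-hour yield rests on one window per patient, always the first, so it is less precise than the recording allows, would absorb any time trend, and tests duration on one patch rather than standard practice

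*Protocol article*

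**What the plan says.** The Abstract (Objective) sets 14 days of patch monitoring "compared to standard practice (a 24- and 48-h long-term ECG" and then defines the comparison: the 14-day frequency "is compared with the frequency in the first 24 or 48 hours for the same patient (intraindividual comparison". Methods, Outcomes fixes the same contrast: "The rate of nsVT detection in the first 24 and 48 hours of monitoring versus the whole 14-day monitoring period will be compared". The first paragraph of the Discussion repeats it. No separate long-term ECG is described as a comparator.

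On timing, Methods, Recruitment says: "A therapeutic procedure is established for the patient based on the information available to date". The next sentence is: "Afterward, an ECG patch is applied to the chest to continuously monitor the heart rhythm over 14 days". After the wearing period, "the therapeutic procedure will be re-evaluated with a recalculation of the HCM Risk–SCD calculator score". The article gives no interval between the therapy decision and the patch, and does not say whether treatment is started or changed at that step.

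Methods, Dropout adds that "a minimum duration of 288 hours has been established"; patients with less are excluded.

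**The concern.** Three features of the contrast matter.

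- **One window where many exist.** Each evaluable patient supplies a dozen or more 24-hour windows, but the stated contrast uses only the first. The estimate of what a short recording would find is noisier than the data require.
- **Window length is tied to calendar position.** The short window is always day 1 or days 1 and 2, so any trend over the 14 days enters the estimated gain. The short window is nested in the long one, so 14-day detection can never fall below first-window detection. The direction is fixed in advance and only the size of the gain is informative, and the size is what a trend would distort.
- **The label is wider than the comparator.** The data compare two durations on one single-channel patch. The Abstract (Objective and Conclusions) and the Discussion speak of standard practice, conventional 48-hour monitoring or long-term ECGs.

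**Working it through.** **1. The plan's own figure.** Statistical Analysis gives 25% against 75% at 14 days, α = 0.05, power 0.8. With the two-sided, uncorrected chi-square formula, n per group = [1.960·√(2·0.5·0.5) + 0.842·√(0.25·0.75 + 0.75·0.25)]² / 0.5² = (1.386 + 0.515)² / 0.25 = 14.5, so 15 per group and 30 in total. 30/0.9 = 33.3, so 34. This reproduces the plan. It rests on the contrast between risk groups, so nothing below changes it.

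**2. Windows available.** 288/24 = 12 and 336/24 = 14; 288/48 = 6 and 336/48 = 7. These are totals that include the first window.

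**3. Illustrative model.** A patient's episode rate is gamma distributed, episodes are Poisson given the patient, and windows are independent given the patient. Then P(no nsVT in t days) = Q(t) = (1 + t/b)^(−a). Inputs:

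- Intermediate risk: 34% at 48 hours (Introduction) and 75% at 14 days (Statistical Analysis) give a = 0.778, b = 2.833.
- Low risk: 25% at 14 days (Statistical Analysis) and 12.5% at 48 hours give a = 0.0889, b = 0.573. The 12.5% is an assumption: half of 25%, from the plan's own doubling argument.
- 15 patients per group, seven 48-hour windows each.

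**4. Standard error of the 48-hour yield.**

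- First window: per-patient variance p(1 − p) = 0.34·0.66 = 0.2244 (intermediate) and 0.125·0.875 = 0.1094 (low). SE = √[15·(0.2244 + 0.1094)]/30 = 7.5 points.
- Mean of seven windows: variance = [p(1 − p) + 6c]/7, with c = 1 − 2Q(2) + Q(4) − p².
  - Intermediate: Q(4) = 0.504, c = 0.0685, variance 0.0908.
  - Low: Q(4) = 0.831, c = 0.0658, variance 0.0720.
  - SE = √[15·(0.0908 + 0.0720)]/30 = 5.2 points.

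**5. Standard error of the 14-day minus 48-hour gain.** Let P be the 14-day prevalence.

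- First window: the gain is an indicator with probability 0.75 − 0.34 = 0.41 (intermediate) or 0.25 − 0.125 = 0.125 (low), with variances 0.2419 and 0.1094. SE = √[15·0.3513]/30 = 7.65 points.
- All windows: variance = P(1 − P) + Var(mean) − 2p(1 − P).
  - Intermediate: 0.1875 + 0.0908 − 0.1700 = 0.1083.
  - Low: 0.1875 + 0.0720 − 0.1875 = 0.0720.
  - SE = √[15·0.1803]/30 = 5.5 points.

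The variance ratio is 0.3513/0.1803 = 1.95. The first-window estimator would need about 30·1.95 ≈ 58 patients for the same precision. A simulation of the same model agrees with steps 4 and 5.

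**6. Sensitivity to a time trend.** Multiply the day 1–2 rate by r, with r = 0.5 and r = 2 as an assumed range. The first-window yield is 1 − Q(2r), the all-window mean is (first + 6·later)/7, and the 14-day yield is 1 − Q(12 + 2r), each averaged over the two groups.

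| r | First-window 48 h | All-window 48 h | 14 days | Gain, first window | Gain, all windows |
|---|---|---|---|---|---|
| 0.5 | 14.8% | 22.0% | 49.2% | 34.4 | 27.1 |
| 1 | 23.3% | 23.3% | 50.0% | 26.8 | 26.8 |
| 2 | 33.2% | 24.7% | 51.5% | 18.2 | 26.8 |

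The 14-day yield hardly moves. The first-window gain runs from about 18 to 34 points, while the all-window gain stays at about 27.

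**The case against.** **The first window is a natural target.** A patient in routine care has one 24- or 48-hour recording. If the rate is stable, the first window estimates its yield without bias. The 14-day study cited in the Discussion reports its 16.9% for the first 24 hours, so this window keeps the results comparable. That stands, and it is why the first-window contrast should stay. The mean over all windows gains efficiency and robustness; it does not repair an error.

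**The comparator is disclosed.** The sentence after the reference to standard practice defines it as the patient's own first hours, and holding patient and device constant is a strength for a question about duration. That also stands. What is left is a matter of wording: the conclusion should carry the same limit as the definition.

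**A reader might infer that monitoring length is confounded with treatment onset.** The documents do not support this. Recruitment says only that the patch comes after the therapy decision, not that it follows at once or that treatment is started or changed. The step may simply record the baseline plan that the change-of-therapy end points need. A trend is possible, but its existence, direction and size cannot be derived from the article.

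**A reader might also expect a larger precision gain.** Applying 75% at 14 days to all 30 patients lowers the standard error of the gain from about 9.0 to 6.0 points. The plan assumes 75% only for the intermediate-risk half, so the figures under the 25%/75% mix are the relevant ones.

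**Estimator detail may belong in an analysis plan that is not shown.** That is fair for the bootstrap. The choice of the first window alone, however, is stated in the article.

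**Conclusion.** The point holds as one of precision, robustness and wording. The stated contrast uses one early window per patient where each evaluable recording holds at least twelve of 24 hours or six of 48 hours. Under the model, using all of them cuts the standard error of the 48-hour yield by about 30% (7.5 to 5.2 points) and that of the gain by about 28% (7.65 to 5.5). These figures rest on the gamma-Poisson form, independence of windows given the patient, full 14-day recordings and the assumed 12.5% low-risk yield. Clustering of episodes over days would reduce the benefit.

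The first-window contrast is not shown to be biased. It would be distorted if the early rate differed from the later rate, and the all-window mean is far less sensitive to that. No separate long-term ECG is described as a comparator, so superiority over one is not tested.

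**What to change.** 1. Keep the first 24-hour and first 48-hour contrasts as stated.
2. Add the 24-hour and 48-hour yield as the patient-level mean over all consecutive, non-overlapping complete windows in the recording. Give the gain to 14 days with a bootstrap interval that resamples patients.
3. Show yield by window position (days 1 to 14, and 48-hour blocks) as a check for trend. If it is flat, the first window and the mean tell the same story; if not, the reader can see it.
4. In the Abstract (Objective and Conclusions) and the Discussion (first and last paragraphs), describe the comparator as 24 or 48 hours of the same single-channel patch, and limit the claim to duration of monitoring.

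The article states that data analysis had not begun. No new data, visit, device or patient is needed, and N = 34 stays. The cost is a slightly more complex estimator and a narrower claim about standard practice.

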**Methods:**

Following the sample size calculation, 34 patients with a low or intermediate risk for SCD, assessed by the HCM Risk–SCD calculator, will need to be recruited in this single-center cohort study between June 2023 and February 2024. All patients will receive an ECG patch that records their heart activity over 14 days. In addition, cardiac magnetic resonance imaging and genetic testing data will be integrated into risk stratification. All patients will be asked to complete questionnaires about their symptoms; previous therapy; family history; and, at the end of the study, their experience with the ECG patch-based monitoring.

**Results:**

The Hypertrophic Cardiomyopathy: Clinical Impact of a Prolonged mHealth-Based Arrhythmia Monitoring by Single-Channel ECG (HCM-PATCH) study investigates the prevalence of nonsustained ventricular tachycardia (ie, ≥3 consecutive ventricular beats at a rate of 120 beats per minute, lasting for <30 seconds) in low- to intermediate-risk patients with HCM (according to the HCM Risk–SCD calculator) with additional mHealth-based prolonged rhythm monitoring. The study was funded by third-party funding from the Department of Cardiology and Intensive Care Medicine, University Hospital Ostwestfalen-Lippe of Bielefeld University in June 2023 and approved by the institutional review board in May 2023. Data collection began in June 2023, and we plan to end the study in February 2024. Of the 34 patients, 26 have been recruited. Data analysis has not yet taken place. Publication of the results is planned for the fall of 2024.

**Conclusions:**

Prolonged mHealth-based rhythm monitoring could lead to differences in the prevalence of arrhythmias compared to 24- and 48-hour long-term ECGs. This may lead to improved identification of patients at high risk and trigger therapeutic interventions that may provide better protection from SCD or atrial fibrillation–related complications such as embolic stroke.

**Trial Registration:**

Deutsches Register Klinischer Studien DRKS00032144; https://tinyurl.com/498bkrx8

**International Registered Report Identifier (IRRID):**

DERR1-10.2196/52035

## Introduction

Cardiac arrhythmias, especially nonsustained ventricular tachycardia (nsVT) and atrial fibrillation (AF), are important comorbidities of hypertrophic cardiomyopathy (HCM) [1,2]. In particular, nsVT is a predictor of sudden cardiac death (SCD) [3,4]. A well-established risk assessment is the HCM Risk–SCD calculator, which queries, among other parameters, the occurrence of nsVT. It is used for recommendations regarding the primary prophylactic implantation of an implantable cardioverter-defibrillator (ICD) [4].

Therefore, adequate screening for nsVT in patients with HCM is highly relevant. It must be assumed that more intensive monitoring can increase the detection rate of cardiac arrhythmias. For example, in one study, a 14-day long-term Holter electrocardiography (ECG) detected nsVT in up to 75% of intermediate-risk patients with HCM. In the same group, a 48-hour long-term ECG revealed nsVT in only 34% of patients [5,6]. In addition, a trial of 100 patients with HCM in Spain showed a 62% rate of nsVT during 30 days of monitoring compared to 8% in the first 24 hours [7]. In another study, 24- to 48-hour long-term Holter ECGs showed at least one AF episode in 23% of patients with HCM [8]. It can be speculated that prolonged ECG monitoring may increase AF detection, leading to the earlier introduction of oral anticoagulants to prevent embolic complications. Patients with HCM with AF have an exceptionally high risk of embolic complications [1].

The feasibility of mobile health (mHealth)–based screening for arrhythmias has not yet been thoroughly investigated in patients with HCM. Holter long-term ECGs and implantable loop recorders are established in everyday clinical practice. Whereas prolonged Holter monitoring is associated with patient discomfort, implantable devices are expensive, have some limitations concerning specificity in arrhythmia detection [9], and carry a risk of surgical intervention for implantation and explantation. More recently, mHealth ECG recorders have become increasingly available, and thus, it should be investigated to what extent mHealth-based prolonged ECG monitoring is feasible and accepted by patients.

In addition to the HCM Risk–SCD calculator, there is increasing evidence that the presence of late gadolinium enhancement and its extent is associated with an increased SCD risk in patients with HCM [10,11]. Furthermore, genotyping is recommended for patients with HCM by the current European Society of Cardiology guidelines since 60% of patients have mutations in cardiac sarcomere protein genes, which have been associated with an increased SCD risk [1,12]. Therefore, we aim to correlate the occurrence and frequency of nsVT associated with late gadolinium enhancement on cardiac magnetic resonance imaging (cMRI) or evidence of a pathogenic mutation. The extent of late gadolinium enhancement on cMRI will be graded as mild (<5%), moderate (5%-15%), or severe (>15%) using a semiquantitative score based on the standard left ventricular 17-segment model.

Prolonged monitoring for cardiac arrhythmias may have relevant implications for clinical decisions, such as primary prophylactic ICD implantation for nsVT and anticoagulation or rhythm-control measures for AF. The extent to which noninvasive prolonged rhythm monitoring through an mHealth ECG patch impacts the detection of cardiac arrhythmias and clinical decisions has not been investigated.

## Methods

### Study Design

The Hypertrophic Cardiomyopathy: Clinical Impact of a Prolonged mHealth-Based Arrhythmia Monitoring by Single-Channel ECG (HCM-PATCH) study aims to investigate the association between the occurrence of cardiac arrhythmias with detected gene mutations and the extent of late gadolinium enhancement in cMRIs. This single-center prospective cohort study will be conducted at the Department of Cardiology and Intensive Care Medicine at the University Hospital Ostwestfalen-Lippe (OWL), Campus Klinikum Bielefeld in Germany. The trial is registered under clinical trial number DRKS00032144 (DRKS-ID).

### Recruitment

According to the sample size calculation (see Statistical Analysis section), recruiting 34 patients will be sufficient for the statistical analysis. Study participants will receive an echocardiography at rest and during exercise (bicycle ergometry) and a cMRI. In addition, their symptoms, family history, and premedication are collected, and their HCM Risk–SCD calculator score will be calculated. According to this score, patients are allocated to three risk groups: low risk (<4%), intermediate risk (4%-6%), and high risk (>6%) of SCD within 5 years. An ICD is generally recommended in the high-risk group, should be considered in the intermediate-risk group, and is not indicated for the low-risk group [1]. For this study, it is planned to recruit 17 patients with low and 17 with intermediate risk scores. All these patients will receive the 14-day ECG patch.

Patients with HCM between the ages of 18 and 75 years will be included if they have not yet undergone implantable loop recorder, pacemaker, or ICD implantation and if their estimated 5-year SCD risk according to the HCM Risk–SCD calculator score is <6%. A maximum age of 75 years was set as the upper limit, as SCD in patients with HCM mainly occurs at a young age [13]. Patients with a pre-existing cardiac implant (pacemaker, ICD, or implantable loop recorder) or an already accepted indication for it; Morbus Parkinson disease with relevant tremor; a transcoronary ablation of septal hypertrophy procedure in the last 4 weeks; inability to give informed consent; and current symptoms or a history of skin cancer, rash from skin adhesive, or dermatoses (contraindication to wearing the patch) are excluded.

A therapeutic procedure is established for the patient based on the information available to date. Afterward, an ECG patch is applied to the chest to continuously monitor the heart rhythm over 14 days. After completing the 14-day wearing period, patients should return the ECG patch. Any arrhythmias recorded will then be documented, and the therapeutic procedure will be re-evaluated with a recalculation of the HCM Risk–SCD calculator score.

An overview of the study process can be seen in Figure 1.

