### Questionnaires

At the beginning of study recruitment, various data such as the patient’s family history, previous syncope or rhythm abnormalities will be collected. In addition, secondary causes for left ventricular hypertrophy, such as arterial hypertension, will be queried. At the beginning and after monitoring completion, we will also ask patients if they have any questions, concerns, or requests they want to address with us. After completion of the 14-day monitoring period, the patient’s perception of the mHealth measure will be evaluated through a questionnaire (Multimedia Appendix 1). This questionnaire is based on the System Usability Scale by Brooke [14], a standardized questionnaire for evaluating utensils.

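### The entry risk score uses nsVT, but no rhythm recording before scoring is described, so re-scoring and therapy changes after the patch may credit prolonged monitoring with nsVT that a 24- or 48-hour ECG would have found

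*Protocol article*

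**What the plan says.** The Introduction describes the HCM Risk–SCD calculator as a tool "which queries, among other parameters, the occurrence of nsVT". Recruitment uses its result twice. Entry requires that "their estimated 5-year SCD risk according to the HCM Risk–SCD calculator score is <6" (per cent), and patients are grouped as "low risk (<4%), intermediate risk (4%-6%), and high risk (>6%) of SCD within 5 years", with 17 low-risk and 17 intermediate-risk patients planned.

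The examinations listed before scoring are these: "Study participants will receive an echocardiography at rest and during exercise (bicycle ergometry) and a cMRI". The same section adds that "their symptoms, family history, and premedication are collected, and their HCM Risk–SCD calculator score will be calculated". Under Questionnaires, "various data such as the patient’s family history, previous syncope or rhythm abnormalities will be collected" at the start of recruitment. A therapeutic procedure is then set on what is known so far, and only afterwards is the patch applied. After 14 days the arrhythmias are documented, the score is recalculated and the procedure is re-evaluated.

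The 24- and 48-hour comparator is the first part of the patch recording (Abstract, Objective; Outcomes). One secondary end point counts patients whose therapy changes because of nsVT found in the additional monitoring (Results). The Discussion sets the aim as detection beyond conventional 48-hour monitoring and the management changes that follow from it.

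**The concern.** For a patient who has never had a long-term ECG, no known nsVT means that nobody looked. The visible text has no rule for entering nsVT in the baseline score in that case. If it is entered as absent, two things follow.

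- **Attribution.** The baseline score lacks information that a 24- or 48-hour ECG would have supplied. The score is recalculated after the full 14 days. An upward re-score, and any therapy change due to nsVT, then counts for the patch as a whole. Part of it may only be the effect of a first recording of any length. The Discussion asks about the gain over 48 hours, not over no recording.
- **Grouping.** Whether a patient is classed as low or intermediate risk may depend partly on whether a Holter ECG had been done before. The sample size rests on the contrast between these two groups.

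**Working it through.** **1. The plan's own figure.** Inputs (Statistical Analysis): 25% against 75% nsVT at 14 days, chi-square test, α = 0.05, power 0.80. Sidedness is not stated; two-sided without continuity correction is assumed.

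n per group = [1.96·√(2·0.5·0.5) + 0.8416·√(0.25·0.75 + 0.75·0.25)]² / 0.50² = (1.386 + 0.515)² / 0.25 = 14.5, so 15 per group and 30 in total. With 10% dropout, 30 / 0.9 = 33.3, so 34. The stated size reproduces and is not disputed.

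**2. Is nsVT status established before scoring?**

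| Step | What the article gives | Establishes nsVT status? |
|---|---|---|
| Examinations | Echocardiography at rest and exercise, cMRI | No rhythm recording listed |
| History | Symptoms, family history, premedication, earlier rhythm abnormalities | Only nsVT already found |
| Prior long-term ECG | Not required in the visible text | Unknown |
| Patch | Applied after scoring and the treatment decision | Too late for the entry score |

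**3. How many patients could be affected?** Expected number = 17 × f × p, where f is the share without an earlier recording (not given, so a range is assumed) and p is the nsVT prevalence on a standard recording.

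- Intermediate risk, 24 h: p = 16.9% (Discussion, for a 14-day Holter study with 75% at 14 days; applying it to this group is an assumption).
- Intermediate risk, 48 h: p = 34% (Introduction).
- Low risk: p = 12.5%, that is 25% / 2, because the plan obtains its 14-day value by assuming a doubling.

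| | f = 25% | f = 50% | f = 100% |
|---|---|---|---|
| Intermediate, 24 h | 0.7 | 1.4 | 2.9 |
| Intermediate, 48 h | 1.4 | 2.9 | 5.8 |
| Low, 24–48 h | 0.5 | 1.1 | 2.1 |

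**4. What share of the apparent gain could this be?** Among never-monitored patients with nsVT by day 14, the share already positive at 48 h is 34 / 75 = 45% in the intermediate group and 12.5 / 25 = 50% in the low group. On the plan's figures, close to half of the newly positive nsVT inputs in such patients would not be due to monitoring beyond 48 hours. How many would change a risk category or a treatment cannot be derived, because the article does not give the weight of nsVT in the score.

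**5. Grouping, illustration only.** Suppose a share m of the nominal low-risk group has the 75% prevalence. Low-group prevalence is then 0.25(1 − m) + 0.75m. With m = 10% it is 30%, and power at 15 per group falls from 0.816 to 0.715. With m = 20% it is 35%, and power is 0.604. The documents give no basis for choosing m.

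**The case against.** The strongest reply is that the documents do not show that recruits lack an earlier recording. The Abstract's Background says that "long-term electrocardiography (ECG) is rarely performed in routine clinical practice". But the same paragraph calls arrhythmia screening mandatory for risk assessment, the Introduction describes Holter ECG as established in daily care, and the Objective treats the 24- and 48-hour ECG as standard. The Results call the patch monitoring additional, which may imply that something came before. Figure 1 and the example table of patient characteristics are not shown and could include a baseline ECG, and an article condenses its protocol. All of this stands: the number affected is unknown and may be small. It does not supply a rule for unknown nsVT or separate the re-scoring results at 48 hours.

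Four stronger readings are tempting but not supported.

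- *The main comparison is biased.* It is not. The first 24 or 48 hours and the 14 days are compared within the same patient, whatever the entry score.
- *Up to 7 of 17 low-risk patients are affected* (17 × 42%). The 42% is the top of a cited range, and 7 exceeds the plan's own 14-day expectation for this group, 17 × 25% = 4.25.
- *Every intermediate-risk patient with unknown nsVT really exceeds 6%.* This needs an nsVT weight that the documents do not give. With an assumed risk multiplier of 1.4, a 4.0% score becomes 5.6%. With a hazard multiplier of 1.5 it becomes 1 − 0.96^1.5 = 5.9%.
- *The groups should be rebuilt from the first 48 hours of the patch.* nsVT on the patch is the primary end point, so early outcome events would define the groups and inflate their contrast.

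**Conclusion.** The point holds in a limited form. The score that governs entry and grouping takes nsVT as an input. The visible text names history as its only source, and the single recalculation after 14 days does not separate what 48 hours would have shown from what came later. The results exposed are re-scoring, therapy change due to nsVT and, less certainly, the low/intermediate contrast.

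The size cannot be fixed from the documents. If nobody had been monitored, about 3 to 6 of 17 intermediate-risk and about 2 of 17 low-risk patients would carry an nsVT input that a standard recording would have corrected. The numbers shrink in proportion to the share already monitored. They rest on the cited 16.9% and 34% and on the plan's assumed doubling to 25%. A reader might infer that patients were wrongly enrolled or that the detection result is unsafe; the documents support neither.

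**What to change.** 1. Record for each patient whether a long-term ECG preceded scoring, with its date and length.
2. Calculate the post-patch score twice, with nsVT from the first 48 hours and with nsVT from all 14 days. Attribute to prolonged monitoring only those re-scores, and those therapy changes due to nsVT, that arise from nsVT first seen after 48 hours.
3. Report re-scoring and therapy-change results separately for patients with and without a prior long-term ECG.
4. Keep the entry risk groups for the risk-group comparison and do not redefine them from patch data.

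The cost is a few case-report-form fields, completed from records for the 26 patients already recruited, and one extra score calculation from data that the patch records anyway. The article states that analysis has not begun, so the rule can still be fixed in advance. The downsides are that the re-scoring gain will look smaller and that the subgroups by prior ECG will be too small for more than description.
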